### Control group

Control group participants will be asked to continue their daily lives normally and maintain regular physical activity during the six-month duration of the study.

### Measurements

Besides the psychological screening baseline at one week after the beginning of training (T1), all participants will be assessed at three months (T2) and six months (T3).Moreover, at the baseline assessment, questions on demographic variables (for example, age, marital status, work, educational level, socioeconomic status), psychiatric history (for example, previous diagnosis of depression and/or anxiety, family history regarding psychiatric diagnosis), and/or health behaviors (for example, alcohol use, smoking habits, physical activity) will be included.

All participating sample were screened for psychological aspects by the following standardized measures:

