**Methods/Design:**

A randomized controlled trial (N = 300) will assess the relative effectiveness of two different exercise programs (whole-body vibration and Multicomponent Training) for improving psychological wellbeing in older-aged women. The following outcomes will be assessed at three time points (that is, pre, post, and follow-up): psychological wellbeing, proactive attitude, quality of life, and happiness.

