### Randomization

Randomization will be performed by statistical experts of the team study using a computerized random number generator at (http://www.randomizer.org/). To obtain equal numbers in both conditions, a block randomization design is chosen. After the completion of the inclusion procedure, the clinical psychologist will obtain the file containing the condition to which the patient is allocated.

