### Interventions

The interventions protocol will consist of six months of training for both groups of vibratory platform and Multicomponent Training. Both groups, WBV and Multicomponent Training, will follow three training sessions per week, with a recovery time between sessions ranging from 24 to 72 hours.

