### WBV training

After the warm-up consisting in eight minutes of static cycling, active stretching and joint mobility, participants will perform the WBV training. The vibration stimulus will consist of uniform vertical oscillations Power Plate® Next Generation (Power Plate North America, Northbrook, IL, USA). Subjects will stand on the platform holding quarter squat positions with the feet shoulder-width apart. Then, they will perform ankle extensions with the following work sequence (establishing a rhythm of 100 bpm: 1 bpm for the concentric phase; and 5 bpm for the eccentric phase). After the familiarization 2-weeks, subjects will train 3 days per week for 6 months (72 sessions) using a vibrating training program that will begin with 5 sets and a frequency of 35 Hz per session and increasing by 11 sets and 40 Hz frequency for the last month, maintaining a series of parameters: vibration amplitude (4 mm) working time (60 seconds) and recovery time (60 seconds).

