## Sample size calculation

In this study, the change in scores in PGWBI and SF-12 are chosen as primary outcome measures to determine the effect of whole-body vibration approach. A difference of 0.5 standard deviations is considered necessary to find a clinically significant effect of the intervention. In order to detect this difference and assuming an 80% power, a minimum of 80 patients is needed in each outcome measure [36]. When assuming that 20% of participants dropout (quite a normal figure in this type of research), a minimum of 23 subjects per condition is needed to maintain sufficient power. We expect that in order to reach such a number, anticipating a response rate of 70% of which 20% is eligible, a total of 300 aged women will need to be screened.

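### The outcome baseline (T1) is written as falling one week after training starts, which conflicts with the abstract and would make the reference for the primary change score post-randomisation

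*Protocol article*

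**What the plan says.** The protocol article gives two accounts of when the outcomes are first measured.

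- **Abstract, Methods/Design:** "The following outcomes will be assessed at three time points (that is, pre, post, and follow-up".
- **Measurements:** "Besides the psychological screening baseline at one week after the beginning of training (T1", after which "all participants will be assessed at three months (T2) and six months (T3".

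Four other places bear on the point.

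- **Randomization:** "After the completion of the inclusion procedure, the clinical psychologist will obtain the file containing the condition to which the patient is allocated". Allocation is therefore out before training starts.
- **Interventions and WBV training:** "Both groups, WBV and Multicomponent Training, will follow three training sessions per week". For vibration, "After the familiarization 2-weeks, subjects will train 3 days per week for 6 months (72 sessions". What the familiarisation consists of, and whether it counts as the beginning of training, is not said.
- **Control group:** these women carry on with usual life, so they have no training start.
- **Sample size calculation:** "the change in scores in PGWBI and SF-12 are chosen as primary outcome measures". The Planned statistical analyses section describes mixed models that set baseline against follow-up.

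The Hypotheses and design section also describes psychologists screening eligible women on wellbeing, proactive attitude and health status. It does not call that screening T1 or name it as the analysis baseline.

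**The concern.** A change score needs a reference that treatment cannot have touched. Read literally, T1 is taken when every woman can know her arm and the two training arms have begun their sessions. The SF-12 and PGWBI are self-administered and subjective, and women cannot be blinded to vibration, outdoor jumping and walking, or no programme. Such scores can move as soon as the arm is known. The change from T1 then measures the effect from week one onward, not the effect of being assigned to the programme.

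The homogeneity check has a related weakness. A difference between groups in T1 psychological scores, or in the physical activity reported at the same assessment, could be an effect of allocation and not chance. A pre-randomisation score that was never collected cannot be recovered later.

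**Working it through.** **1. Do the two timings agree?** They do not. A pre-training measurement and one a week into training are different things. The abstract's labels cannot simply be used to correct the Measurements section, because its later labels do not fit either. Training lasts six months, so T2 at three months is mid-training and T3 at six months is at about the end. No assessment after the end of training is described that would match a follow-up.

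**2. What has happened by T1, as written?**

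| | WBV | Multicomponent | Control |
|---|---|---|---|
| Randomised, allocation released | yes | yes | yes |
| Training contact by T1 | yes | yes, about 3 sessions (3 per week × 1 week) | none |
| Training start that dates T1 | ambiguous (familiarisation counted or not) | defined | undefined |

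If training begins with the WBV familiarisation, T1 falls in the middle of it. If training begins afterwards, T1 falls after two weeks of familiarisation plus about three sessions. T1 follows first contact with the programme on either reading.

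**3. How an early difference enters the estimate.** Let D be the true difference between two arms at T3, relative to a true pre-randomisation baseline. Let e be the difference already present at T1. The expected difference in change scores is D − e. Writing e = f × D gives D × (1 − f). For WBV against control, e is the full early response to training and allocation. For WBV against Multicomponent, a response shared by both training arms cancels, and e is only the part that differs.

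**4. The plan's own figure.** Inputs from the Sample size calculation are a difference of 0.5 SD, 80% power and a minimum of 80. The 0.05 level is in the Planned statistical analyses; two-sided is assumed. A two-sample t-test needs 63.8, so 64 per arm. Since 64 / 0.8 = 80, the figure of 80 is reproduced per arm only if it already includes the 20% dropout. The section applies dropout after the 80 and then gives 23 per condition, so the number analysed is unclear. That is a separate matter. Here it means that any n used for illustration is an assumption.

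**5. Illustration.** D = 0.5 SD, with the SD taken as that of the change score; two-sided 5% t-test. The fraction f is assumed, because the article gives nothing from which to derive it. The one value tied to the trial's timing is linear accrual: 1 week of 26 = 0.038, about 4%.

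| f | Expected difference (SD) | Power, 80 analysed per arm | Power, 64 analysed per arm |
|---|---|---|---|
| 0 | 0.500 | 88% | 80% |
| 4% (1/26) | 0.481 | 86% | 77% |
| 10% | 0.450 | 81% | 71% |
| 25% | 0.375 | 65% | 56% |
| −10% | 0.550 | effect overstated | effect overstated |

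At 80 per arm the linear-accrual case costs 88.2 − 85.6 = 2.6 percentage points.

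**The case against.** The strongest reply is that the sentence is a slip, with after written for before. Much supports this. The abstract speaks of a pre assessment, psychologists screen eligible women on the same constructs, allocation is released only once inclusion is complete, and the Measurements section itself calls T1 a screening baseline. That reading is plausible, and the point is therefore stated as a conflict to be resolved. It does not remove the need for the correction, because the sentence that site staff would follow gives the later timing and no other passage defines an outcome baseline.

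The second reply is that the harm may be small. This also stands in part. Under linear accrual the loss is under 3 points of power, and nothing in the article supports a quarter of a six-month effect appearing within a week. The larger rows in the table show sensitivity and are not forecasts.

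A reader might infer three stronger things that the document does not support.

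- **That the trial's baseline is known to be contaminated.** The article leaves the intended timing open.
- **That the effect is bound to be understated.** Early soreness or burden in the training arms would lower T1 and overstate the change. In WBV against Multicomponent, only a differential early response matters.
- **That the whole baseline comparison is invalid.** Age, marital status, education and psychiatric history are not altered by a week of training. Only the psychological scores and reported physical activity are exposed.

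**Conclusion.** The timing of T1 is internally contradictory and has no meaning for the control arm. If followed as written, it gives a post-randomisation reference for the primary change in PGWBI and SF-12, and any difference between arms at T1 passes in full into the change-score contrast. The bias is absent only if the arms do not differ at T1, which the design as written cannot show.

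The size and sign of that bias cannot be derived from the article. The power figures rest on an assumed 80 (or 64) analysed per arm, a two-sided 5% test, 0.5 SD on the change scale and assumed values of f. The case for correction does not depend on them. It rests on a primary endpoint whose baseline is contradictory as stated, a low cost of correction and a loss that cannot be made good after enrolment.

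**What to change.** Reconcile the abstract, the screening description under Hypotheses and design, and the Measurements section with one definition. T1 is collected in all three arms before randomisation, before the allocation is disclosed and before any familiarisation session. State that this score is the analysis baseline for the primary change and the mixed models, and that the homogeneity check uses data from this assessment. Align the abstract's labels for the later assessments with three and six months.

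The cost is that one assessment moves earlier. The screening contact can host it, so there is no extra visit or questionnaire.

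If T1 has already been collected as written, compare T2 and T3 between arms without subtracting or adjusting for T1, and use only covariates fixed before randomisation. That keeps the randomised comparison but gives up the precision that a true baseline would have brought.

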#### *Primary outcome measures*

**SF-12 Health Survey** It is a self-administered test that assesses the global health status by the subjective point of view of the subject. It has been divided into two principal subscales: the Physical Component Summary (PCS) and the Mental Component Summary (MCS). In particular, it allows the assessment of concepts concerning health, physical functions, pain, general health, vitality, social functioning, emotional functioning and mental health [32].

#### The Psychological General Well-Being Index (PGWBI)

It is a self-administered test with 22 items that assesses the subjective sensation of psychological wellbeing. It has been divided intosix categories: anxiety, depression, self-control, positivity and wellbeing, health and vitality [33].

### *Secondary outcome measures*

**Subjective Happiness Scale (SHS)** It is a four-item scale for assessing subjective happiness. Two items ask respondents to characterize themselves using both absolute ratings and ratings relative to peers, whereas the other two items offer brief descriptions of happy and unhappy individuals and ask respondents the extent to which each characterization describes them. The SHS has been validated in 14 studies with a total of 2,732 participants. Preliminary results have indicated that the SHS has high internal consistency, which has been found to be stable across samples. Test-retest and self-peer correlations have suggested good to excellent reliability, and construct validation studies of convergent and discriminant validity have confirmed the use of this scale to measure the construct of subjective happiness [34].

### 

**Proactive Attitude Scale (PA)** It assesses the presence of a proactive attitude that is a relatively persistent personal belief in the rich potential of changes that can be made to improve oneself and one’s environment. The proactive attitude has implications for motivation and action. This includes various facets such as resourcefulness, responsibility, values and vision. The psychological construct of Proactive Attitude (PA) presents a correlation of r = .56 with general self-efficacy [35].

## Ethical principles

The study of this protocol will not involve the administration of drugs. However, the investigator will be responsible for ensuring that the study will be conducted in accordance with the principles defined by the 18th World Medical Assembly (Helsinki, 1964) and subsequent amendments established by the 29th (Tokyo, 1975), 35th (Venice, 1983), 41st (Hong Kong, 1989), and the 48th World Medical Assembly (Somerset West, South Africa, 1996), and 52nd (Edinburgh, Scotland, 2000) General Assembly. The study will also be conducted in accordance to the Ministerial Decree of 15 July 1997 transposing the text of the rules of Good Clinical Practice for human trials of medical products within the EEC. At the time this manuscript was submitted, full approval by the Human Subjects Ethics Committee of the Universidad Católica San Antonio de Murcia had been obtained.

## Planned statistical analyses

The demographic and clinical characteristics of the three study groups will be compared at baseline to verify their homogeneity. To do this, analysis of variance (ANOVA) for continuous variables and chi-square test of Mantel-Haenszel test for discrete variables will be used. Complete and intent-to-treat analysis will be accomplished to compare primary outcome treatments. First, prevalence of happiness, proactive attitude, psychological wellbeing and quality of life will be displayed infrequency tables and both conditions (control and intervention)will be compared using the chi-square (Fisher’s exact test when appropriate) and Student’ s *t*-test, for discrete and continues variables respectively. The effect of the intervention will be determined using multilevel analyses (mixed effect regression models) to compare baseline and follow-up measures of all continuous data. In all these analyses a *P*-value of <0.05 will be considered statistically significant.

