## Methods/Design

### Hypotheses and design

Starting from current literature, we hypothesize that specific physical activity, WBV, may promote psychological wellbeing and quality of life in female aged subjects, if compared with Multicomponent Training program and normal physical activity. Therefore, we assume an improvement in proactive attitude, quality of life, wellbeing and happiness of WBV training group when compared to and Multicomponent Training and control group.

The comparison among WBV group, Multicomponent Training group and control group will be assessed in a three-arm randomized controlled clinical trial (Figure 1).

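### The simple outcome tests and the randomisation are worded for two conditions in a three-arm trial, and no sentence commits to comparing WBV with Multicomponent Training

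*Protocol article*

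**What the plan says.** Under Hypotheses and design, the article says: "The comparison among WBV group, Multicomponent Training group and control group will be assessed in a three-arm randomized controlled clinical trial". The hypothesis in the same section is that the WBV group improves "when compared to and Multicomponent Training and control group". The Abstract gives the aim as the relative effectiveness of the two exercise programmes, and the intervention sections describe two separate training groups plus a control group.

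Randomization then reads: "To obtain equal numbers in both conditions, a block randomization design is chosen".

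Planned statistical analyses begins with three groups: "The demographic and clinical characteristics of the three study groups will be compared at baseline to verify their homogeneity", using ANOVA for continuous variables. For the outcomes it changes to two: "both conditions (control and intervention)will be compared using the chi-square" (or Fisher's exact test) for discrete variables and Student's t-test for continuous ones. It goes on: "The effect of the intervention will be determined using multilevel analyses (mixed effect regression models) to compare baseline and follow-up measures", for continuous data only. The significance level is 0.05 throughout, and sidedness is not stated.

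**The concern.** The hypothesis has two parts, WBV against control and WBV against Multicomponent Training. A test between control and intervention can address at most the first. This is more than an omission that a fuller document would supply, because the article does specify a comparison, and it is one that does not match its own design. An analysis plan that followed it would leave the head-to-head question unanswered.

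If intervention is taken to mean both exercise arms together, there is a second cost. A significant result could not be attributed to WBV, and an effect of WBV alone would be diluted by the other arm.

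**Working it through.** **1. The contradiction, without arithmetic.** The design section has three arms and two contrasts, both involving WBV. The baseline comparison has three groups. The outcome tests have two conditions, one of them control. There are two main ways to read intervention:

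- Both exercise arms pooled: the test is exercise against control.
- WBV alone: the test is WBV against control, and the Multicomponent arm drops out of these tests.

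On either reading, WBV is not compared with Multicomponent Training. The mixed model names a single intervention effect, no three-level group factor and no WBV contrast. It does not cover discrete outcomes, for which the two-condition test is the only one given.

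**2. What pooling would do (first reading only).**

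Inputs from the documents: an effect of 0.5 SD (Sample size calculation) and a significance level of 0.05.

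Assumptions: two-sided tests, equal arms of n, within-arm SD of 1. The small extra spread from mixing two arms with different means is ignored.

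The per-arm number is also uncertain, so a range is shown:

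- 23 is the article's figure per condition.
- 64 is the two-sided t-test requirement for 0.5 SD at 80% power.
- 80 is the article's other figure, read here as per arm (64/0.8 = 80).
- 100 is 80/0.8, and also one third of the Abstract's N = 300.

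Formulas:

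- Pooled difference = (WBV effect + Multicomponent effect)/2. Its standard error is √(1/n + 1/(2n)) = √(1.5/n).
- Single WBV contrast: standard error √(2/n).
- Both WBV contrasts significant: bivariate normal with correlation 0.5, because the WBV arm is shared.

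Worked at n = 80:

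- Only WBV works: the pooled difference is (0.5 + 0)/2 = 0.25. The standard error is √(1.5/80) = 0.137, the ratio is 1.83, and t-test power is 44%.
- Single WBV contrast: 0.5/√(2/80) = 3.16, power 88%.
- Both programmes work at 0.5 SD: the pooled difference is 0.5, 0.5/0.137 = 3.65, and the test is positive 95% of the time.

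| n per arm | Pooled test, only WBV works | One WBV contrast | Both WBV contrasts | Pooled test, both programmes work equally |
|---|---|---|---|---|
| 23 | 16% | 38% | 24% | 49% |
| 64 | 37% | 80% | 70% | 90% |
| 80 | 44% | 88% | 81% | 95% |
| 100 | 53% | 94% | 90% | 98% |

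The third and fourth columns assume that WBV is 0.5 SD better than each comparator. The fourth uses the normal approximation and the others the t-test. By symmetry, the second column also gives the chance of a positive pooled test when only Multicomponent Training works.

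**3. Two contrasts at 0.05 each.** If either one could count as success, the familywise error is 1 − P(|Z₁| < 1.96 and |Z₂| < 1.96) with correlation 0.5, which is 9.1%.

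**4. Size needed for both contrasts.** 80% power for both at 0.5 SD needs 79 evaluable per arm. With 20% dropout, 79/0.8 = 98.75, so 99 are randomised per arm, or 3 × 99 = 297 in total.

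**The case against.** The strongest reply is that the chi-square and t-tests are only a first step, set beside frequency tables, and that the article assigns the effect analysis to the mixed model. Nothing limits that model to two groups, the same section speaks of three study groups, and an article commonly leaves model contrasts to a fuller document. This stands in part. A reader might infer that the plan is unable to test its own hypothesis, but the text does not support that, because a three-level group factor would fit the planned model. What remains is that the only outcome comparison the article spells out is between two conditions, and the model sentence repeats the single intervention without naming a WBV contrast.

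A reader might also infer that the two exercise arms will be merged. No sentence says so, and Sample size calculation ties the primary outcomes to the effect of WBV. If intervention means WBV alone, nothing is diluted and the pooled figures do not apply, but the head-to-head comparison is still absent.

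Finally, a reader might conclude that the blocks will balance two groups rather than three. That is not established. Randomization does not say which two conditions it means and gives no block size, and Interventions uses similar two-group wording for the two training arms. Allocation wording would not in any case make a contrast untestable. As written, though, it does not describe a three-arm allocation.

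**Conclusion.** The point holds as a contradiction between the three-arm hypothesis and the two-condition wording of the outcome tests and the randomisation. The stated chi-square and t-tests leave out WBV against Multicomponent Training on either reading of intervention, and no other sentence commits to that comparison. This conclusion does not depend on the sample size.

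The size of the consequence is conditional on pooling, two-sided testing and equal arms. Over 23 to 100 per arm, pooling gives 16% to 53% power where one direct contrast gives 38% to 94%. It gives a positive result 49% to 98% of the time when both programmes work equally and half of the hypothesis is false. Across that range, a positive pooled result does not separate the hypothesis from its failure. The wording should be corrected before the analysis is fixed, because it decides whether the head-to-head part of the hypothesis is tested.

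**What to change.** In Planned statistical analyses, replace the two-condition tests by two named contrasts, WBV minus control and WBV minus Multicomponent Training. Estimate them from the planned mixed model with a three-level group-by-time term, and make the same two pairwise comparisons for discrete outcomes. State how they combine: both must be significant at 0.05 for the full hypothesis, or alpha is shared if either may count (for example 0.025 each). Label any pooled exercise-against-control comparison as descriptive.

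In Randomization, replace the reference to two conditions by equal allocation to the three arms, with block sizes that are multiples of three.

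This is a change of wording in two sections and requires no new measurements. The downside is that power to show both contrasts is lower than for one (for example 81% against 88% at 80 per arm, 24% against 38% at 23) and should be stated as such. Which per-arm number applies has to be settled in Sample size calculation, where the figures do not agree with each other.

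### The sentence defining the intervention effect names a baseline-to-follow-up comparison, and the only stated between-group outcome test is unadjusted and covers two conditions in a three-arm trial

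*Protocol article*

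**What the plan says.** Under Hypotheses and design, the arms "will be assessed in a three-arm randomized controlled clinical trial", and the expected result is an "improvement in proactive attitude, quality of life, wellbeing and happiness of WBV training group when compared to and Multicomponent Training and control group". That is two contrasts: WBV against Multicomponent Training, and WBV against control.

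Planned statistical analyses opens its outcome part with a between-treatment aim: "Complete and intent-to-treat analysis will be accomplished to compare primary outcome treatments". Two steps follow.

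- First, outcomes are tabulated and "both conditions (control and intervention)will be compared using the chi-square (Fisher’s exact test when appropriate"), with Student's t-test for continuous variables. No baseline adjustment is mentioned.
- Then the intervention's effect "will be determined using multilevel analyses (mixed effect regression models) to compare baseline and follow-up measures". This is the only sentence that says how the effect is obtained.

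The section applies one significance threshold, 0.05, to every analysis it lists. Sample size calculation adds that "the change in scores in PGWBI and SF-12 are chosen as primary outcome measures". Measurements places the T1 baseline one week after training starts, with T2 at three months and T3 at six.

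**The concern.** A comparison of baseline with follow-up is a time effect. Randomisation supports a different quantity, the difference between arms in the outcome or in its change. An analyst who followed the sentence literally could report that WBV participants improved and credit the programme with movement shared by all arms, such as retest effects, season or regression to the mean. Naming change in score as the primary outcome makes that reading easier.

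The between-group test that is spelled out does not close the gap. It has two conditions where the trial has three arms, so half of the hypothesis is left without a stated outcome test. As written it also makes no use of each woman's own baseline score, which costs precision.

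**Working it through.** **1. Hypothesis against stated tests.**

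| Contrast in the hypothesis | Outcome test stated |
|---|---|
| WBV vs control | Unadjusted t-test or chi-square, if the intervention condition means WBV |
| WBV vs Multicomponent Training | None |
| Either, as a difference in change over time | Mixed model, but only baseline vs follow-up is named |

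**2. The plan's own sizing.** Inputs from Sample size calculation: "A difference of 0.5 standard deviations is considered necessary to find a clinically significant effect of the intervention", and "assuming an 80% power, a minimum of 80 patients is needed in each outcome measure". Two-sided 0.05 is assumed. Per arm, n = 2(1.960 + 0.842)²/0.5² = 2 × 7.85/0.25 = 62.8, so 63 (64 with the t distribution). 64/0.8 = 80, so 80 matches only as a per-arm number that already allows for 20% dropout. The text instead applies dropout after the 80 and arrives at 23 per condition. That mismatch is a separate matter. What counts here is that the calculation contains no baseline-to-follow-up correlation, so it does not show which contrast was meant.

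**3. Precision of three ways to contrast two arms.** Let r be the baseline-to-T3 correlation, with equal SDs at both visits. The document gives no r, so 0.3 to 0.7 is assumed. Variance relative to the unadjusted T3 comparison is 2(1 − r) for a change score and 1 − r² with baseline adjustment. The ratio of adjusted to change score is (1 − r²)/[2(1 − r)] = (1 + r)/2.

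| r | T3 only | Change score | Adjusted | Adjusted vs T3 only | Adjusted vs change |
|---|---|---|---|---|---|
| 0.3 | 1 | 1.40 | 0.91 | 9% lower | 35% lower |
| 0.5 | 1 | 1.00 | 0.75 | 25% lower | 25% lower |
| 0.7 | 1 | 0.60 | 0.51 | 49% lower | 15% lower |

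For 0.5 SD at 80% power, before dropout, the number per arm is 63 for T3 only. For the change score it is 88, 63 and 38 at r = 0.3, 0.5 and 0.7, and with adjustment 58, 48 and 33. With 64 analysed per arm, power is 0.807 for T3 only; 0.667, 0.807 and 0.955 for the change score; and 0.843, 0.904 and 0.977 adjusted.

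**4. Where the mixed model falls.** With complete data, free baseline means and an arm-by-visit term, its T3-minus-baseline contrast is the change-score column. With one common baseline mean it is about as efficient as the adjusted column. The article does not say which applies.

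**5. Illustration of the before-after reading.** Suppose both arms drift by 0.2 SD with no difference between them, r = 0.5, and 64 are analysed per arm. The SD of change is √[2(1 − 0.5)] = 1, so z = 0.2 × √64 = 1.6. The chance of a significant within-arm change is Φ(1.6 − 1.96) = 0.359. WBV is significant and control is not with probability 0.359 × 0.641 = 0.230. The drift is assumed, and the plan announces no arm-by-arm tests.

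**The case against.** The best defence is that the clause is compressed and should be read in context. The hypothesis is between arms, the analysis section says treatments will be compared, and a model said to determine an intervention effect would ordinarily contain arm. An article may leave the arm-by-visit term, the covariates and the visit of interest to the full protocol or analysis plan. The t-tests come first, beside frequency tables, so they need not be the main analysis. A change-score contrast is valid under randomisation.

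Much of this stands, and it rules out three stronger conclusions that a reader might draw:

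- **That the plan replaces the between-arm comparison with a before-after one.** The stated aims say otherwise, and no within-arm testing is announced. The probability in step 5 shows the hazard of a misreading and does not describe the plan.
- **That baseline is never used.** A mixed model that includes baseline measures uses them. Only explicit adjustment is unstated.
- **That the mixed model wastes precision.** The loss is shown for the unadjusted tests and for a plain change-score contrast, at an assumed r. It is not shown for a model with a common baseline mean.

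What the defence does not remove is that the article states a comparison, and the one stated is not the randomised contrast. Nor does condensation explain a two-condition test in a three-arm trial. Those tests also fall under the same 0.05 threshold, so nothing marks them as descriptive.

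**Conclusion.** The point holds as a defect in how the effect is defined. The defining sentence names time and not arm, and WBV against Multicomponent Training has no stated outcome test. This follows from the text and needs no assumption.

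The precision gain depends on r, which is assumed, and on equal SDs at both visits. Over r = 0.3 to 0.7, adjustment lowers variance by 9% to 49% against the unadjusted T3 test and by 35% to 15% against a change score. If the intended model already constrains baseline means to be equal, the gain is nil and only the wording needs repair.

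**What to change.** State the primary analysis of each primary scale as a mixed model in one of two forms:

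- T2 and T3 scores as responses, with arm, visit, arm-by-visit and that scale's pre-randomisation score as covariate; or
- baseline, T2 and T3 scores as responses, with one common baseline mean across arms.

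Define the effect as the WBV-control and WBV-Multicomponent differences at T3. Label the t-tests and chi-square tests descriptive, and say what the two conditions are.

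Before that, reconcile the timing of T1. A score taken a week into training follows randomisation and may already reflect the intervention, so it should not be the covariate. A change score measured from T1 has the same difficulty. Hypotheses and design mentions psychological screening when women are approached, but does not say that it yields a score on every outcome scale.

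If a pre-randomisation score exists for each scale, the cost is wording only and no new data are needed. If not, the timing of the baseline questionnaires has to be settled as well.
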